# Trial Participants

## Overall Description of Trial Participants

The trial will enrol adults (≥ 18 years old) admitted to the Hospital for Tropical Diseases, Ho Chi Minh City. Patients should have a suspected diagnosis of TBM, as judged by the attending physician according to local guidelines, and require anti-tuberculosis treatment. Published diagnostic criteria will be used to categorise participants retrospectively into definite, probable, or possible TBM once the results of all investigations have returned (see appendix C)^24^.

## Inclusion Criteria

- Male or Female, aged 18 years or above.
- Suspected TBM and anti-tuberculosis chemotherapy either planned or started
- Less than 3 days of anti-tuberculosis chemotherapy taken for the current infection
- Patient or representative (if the patient is unable) is willing and able to give informed consent for participation in the study.

## Exclusion Criteria

Patients may not enter the study if ANY of the following apply:

- HIV infection (negative rapid test or Elisa test is required)
- They are unlikely, for any reason, to be able to have an MRI brain scan within 5 days (120 hours) of randomisation
- Known or suspected infection with multi-drug resistant tuberculosis (resistant to at least isoniazid and rifampicin)
- Unable to take isoniazid, rifampicin, or pyrazinamide at recommended doses for any reason
- History of diagnosed peptic ulceration or gastro-intestinal bleeding
- Active gastro-intestinal bleeding is suspected
- Taken >1 dose of aspirin (at any dose) or any other NSAID for any reason within 2 weeks of screening
- Aspirin considered mandatory for any reason by the attending physician
- Aspirin considered to be contraindicated for any reason by the attending physician
- Pregnancy or breast feeding (negative urine pregnancy test for all females of child-bearing age)
- Dexamethasone considered to be contraindicated for any reason by the attending physician .
- Any other significant disease or disorder which, in the opinion of the Investigator, may either put the participants at risk because of participation in the study, or may influence the result of the study, or the participant’s ability to participate in the study.

## Study Procedures

### Identification of Potential Participants

All patients with suspected TBM according to local guidelines will be identified for screening by the ward doctors. As a part of clinical care patients will have a lumbar puncture, and when possible, a GeneXpert MTB/RIF test on CSF to assess likelihood of infection with multi-drug resistant tuberculosis. The results of these tests will be available for study screening.

### Informed Consent

Informed consent will be taken by the attending doctors, all of whom will receive specific training in the study and will be authorised to take consent by the trial PI. These doctors will also assess whether or not the patient has mental capacity to provide informed consent. If the doctor judges that the patient does not have this capacity (for any reason, but most likely to be confusion or coma secondary to TBM), they will obtain informed consent from the patient’s representative (usually a relative).

It must be made completely and unambiguously clear that the patient (or their representative) is free to refuse to participate in all or any aspect of the trial, at any time and for any reason, without incurring any penalty or affecting their treatment.

The informed consent form will be presented to the participants or representatives detailing no less than: the exact nature of the study; the implications and constraints of the protocol; the known side effects, risks involved and alternatives to taking part. Those who refuse consent will be treated as per the best available standard of care and will not have any study related procedures performed.

The patient or their representative must personally sign and date two of the latest approved version of the informed consent form. The study staff will also sign and date the two copies.

If the patient/representative is illiterate, a witness who is not a member of the study staff will be present during the informed consent discussion. The informed consent form will be read to the patient/representative in the presence of the witness. If the patient/representative agrees to participate, the form will be signed and dated by the witness.

If consent is provided by a representative and the patient regains the capacity to consider participation during the study period, the patient should be consulted and informed consent to continue the study obtained. If the patient refuses to give informed consent to participate s/he will be withdrawn from the study without compromise to their clinical care.

### Screening and Eligibility Assessment

Potential participants will be screened by the attending physicians. Screening will include the CSF analysis results of the standard diagnostic lumbar puncture and GeneXpert MTB/RIF test when available. Any residual volume of CSF remaining from this lumbar puncture will be stored for the purposes of this study. The results of an HIV test (performed routinely on all patients admitted to the ward) will also be available at screening. Results of any tests performed for clinical care during this illness episode may be used for the purposes of screening. Residual volumes of samples drawn for clinical care during this illness episode may be tested or stored for analysis detailed in this protocol. Results of tests on cerebrospinal fluid obtained within 7 days of randomization and results on blood obtained within 2 days of randomization may be applied to meet inclusion/exclusion criteria.

A screening log will be kept on the ward, with a record of all patients screened and how they met/did not meet the study entry and exclusion criteria. Patients who do not meet the study criteria will be informed as such and treated as per best available clinical care.

### Baseline Assessments

Eligible patients will be carefully assessed clinically at baseline, with special attention paid to the duration of illness, Glasgow coma score, and focal neurological deficit. The results of all diagnostic lumbar punctures and relevant tests will be recorded. MRI brain should be performed as soon as possible and within 5 days of randomisation if not previously performed within the 5 days prior to randomisation.

Blood (5mls) will be taken from all patients and stored for later testing of host genetic polymorphisms which may influence disease pathogenesis and response to treatment, including LTA4H. Patients will have 20mls heparinised blood taken at baseline for isolation of peripheral blood mononuclear cells and the subsequent assessment of the antimicrobial activity of the monocytes/macrophages.

If the patient has not already started anti-tuberculosis drugs, these should be initiated immediately along with adjunctive dexamethasone (recommended for all patients with TBM). The clinical condition of the patient, together with the results of prior CSF analysis should be recorded in the clinical record form (CRF).

### Randomisation and Dosing

Randomisation will be 1:1:1 to 81mg aspirin, 1000mg aspirin and placebo, with stratification by MRC disease severity grade. Subject numbers will be stratified and assigned sequentially as each subject is randomised. Each patient will receive the next sequential package of blinded study drugs which will be prepared in advance and available on the ward. Each treatment pack will contain two bottles of study treatment. One bottle will contain 81mg tablets of aspirin or placebo, the second bottle will contain 500mg tablets of aspirin or placebo. For 60 days, patients will take one 81mg tablet and two 500mg tablets. Administration of the two daily 500mg tablets will be separated by approximately 12 hours.

The first dose of one 81mg tablet and one 500mg tablet will be given as soon as possible after randomisation. One 500mg tablet will be taken approximately 12 hours later. In the case of the first dose being taken late in the day on study day one, the second dose may be given over a shorter time period to ensure the full dose is administered on the first day.

Patients will take medication orally with water if required. Patients unable to swallow will be given crushed tablets via a naso-gastric tube at the same doses.

Patients who vomit within 30 minutes of dosing will be given a replacement dose.

### Subsequent Assessments

The outline of study assessments is provided in appendix B.

Follow-up clinical assessments should be made weekly until discharge from hospital. The assessments will include careful neurological examination and proactive surveillance for symptoms and signs of aspirin toxicity/adverse reactions (e.g. gastritis, tinnitus, gastrointestinal bleeding, renal impairment). All adverse events will be documented, followed and assessed for the likelihood of being related to aspirin.

A full blood count, and measurement of plasma urea, creatinine, electrolytes and stool microscopy for red blood cells will be taken on each clinical assessment day, day 30 and day 60 (5mls EDTA blood; 5mls clotted blood). Patients will have 20mls of heparinised blood taken at day 240 for assessment of the antimicrobial activity of peripheral blood monocytes/macrophages. Whole blood (2ml) will be obtained at 5 time points during the first 14 days of study treatment and analysed to assess the pharmacokinetic characteristics of aspirin.  Time points will be randomly assigned to a range of periods after drug dosing. A concentration-time profile of salicylic acid including exposure, peak levels, half-life, elimination clearance and volume distribution will be analysed.

Patients will have lumbar punctures on days 30 and 60, as per normal clinical care of patients with TBM in the hospital. 10mls of CSF should be taken when possible (as per normal care) and standard biochemical and microbiological tests performed (including mycobacterial smear and culture and GeneXpert MTB/RIF on all specimens collected during the study period). The CSF supernatant should be stored immediately at -80^0^C for later analysis of cytokine and eicosanoid concentrations.

A full clinical examination, brain MRI and neurological disability assessment by the Glasgow coma score and the Modified Rankin score will performed on days 60 and 240.

Window periods for all study procedures will be: +/- 2 days for any procedure scheduled for day 7, 14, 21, 28; +/- 5 days for any procedure scheduled on day 30 – 60; and +/- 14 days for any procedure scheduled for day 240. Screening, enrolment and day 1 schedule windows are as detailed in the appropriate sections of this document.

Published diagnostic criteria will be applied to all enrolled patients at discharge or death, and when all mycobacterial culture results are available (see appendix C). The criteria will sub-divide all cases into definite, probable and possible tuberculous meningitis, and those with an alternative diagnosis.

## Discontinuation of Treatment and Participation

If a patient or the representative who has given consent on their behalf, chooses to discontinue trial treatment, they should be followed up (providing they are willing) and encouraged to follow the study procedures in lieu of withdrawing from the trial. If they do not wish to remain on trial follow-up, however, their decision will be respected and the patient will be withdrawn from the trial completely. This will be recorded on the OUTCOME CRF. The reason for the patient withdrawing should be ascertained wherever possible. Prior to withdrawing completely from the trial, the patient will be invited to have assessments performed as appropriate for the final visit although they would be at liberty to refuse any or all individual components of the assessment.

In addition, the investigator may discontinue the study drug at any time the investigator considers it necessary for any reason including those below. These patients will continue to be followed according to the study protocol.

- A serious adverse event related to aspirin
- Pregnancy
- Ineligibility (either arising during the study or retrospective having been overlooked at screening e.g. an alternative diagnosis to TBM being confirmed)
- Significant protocol violation
- Significant non-compliance with treatment regimen or study requirements

# STUDY TREATMENT

## Description of Study Treatment

An independent trial pharmacist will generate a randomization list stratified by site and MRC grade, with treatment assignments in blocks of varying size. Based on this list, identical treatment packs will be created and distributed to the wards. Each treatment pack will contain two bottles. The first bottle will contain 60 tablets of either 81mg aspirin or matched placebo. The second bottle will contain 120 tablets of either 500mg aspirin or matched placebo. Additional pills will be added to bottles to allow for accidental discards, replacement of vomited doses and to limit manipulation of compliance pill counts. All patients will take one 81mg tablet and two 500mg tablets per day. Administration of the two daily 500mg tablets will be separated by approximately 12 hours. Treatment allocation will be as follows:

Arm A: 81mg aspirin – one tablet 81mg aspirin, two tablets 500mg-matched placebo (bottle #1 is aspirin, bottle #2 is placebo)

Arm B: 1000mg aspirin – one tablet 81mg-matched placebo, two tablets 500mg aspirin (bottle #1 is placebo, bottle #2 is aspirin)

Arm C: placebo – one tablet 81mg-matched placebo, two tablets 500mg-matched placebo (bottle #1 and #2 are placebo)

Daily treatment of one 81mg size tablet and two 500mg size tablets (1000mg in two divided doses) will be taken for 60 days.

The 81mg tablets and 500mg tablets will not be visually matched, hence the need for patients to take both tablets for each dose. All tablets will be coated to prevent taste differentiation between active drug and placebo.

## Storage of Study Treatment

Aspirin and placebo are stable at room temperature for 24 months.

## Compliance with Study Treatment

For the first 14 days of treatment, the drug will be administered under observation of the ward nurses thus ensuring compliance with the regimen. Patients may be discharged after day 14 and may complete study drug treatment at home. Compliance inquiry and counselling will be done at each study visit by the study staff. Patients will be instructed to return all medication and bottles at the day 60 visit when a pill count will be done. Medication bottles of patients who die or withdraw will be collected when possible for compliance and inventory checks.

## Accountability of the Study Treatment

All receipt, transfers, dispensing, administration and return of study drug will be accounted for by the trial pharmacist. Study drug will be prescribed and administered by standard hospital and OUCRU procedures. Ward nurses trained in study procedures will be responsible for safe storage and in-hospital administration.

## Prophylaxis

Prophylaxis against upper gastro-intestinal symptoms and bleeding is recommended. Patients will be prescribed ranitidine (300mg at night) unless the attending physician decides otherwise. Antacids should be avoided, if possible, as they may increase the urinary excretion of aspirin. Proton pump inhibitors (e.g. omeprazole) should also be avoided as they interact with rifampicin.

## Concomitant Medication

Throughout the study, Investigators may prescribe any concomitant medications or treatments deemed necessary to provide adequate supportive care, with the exception of other NSAIDS.

Study doctors should also be aware of the following potential interactions noted in the aspirin summary of produce characteristics (SPC):

- Aspirin may enhance the effects of anticoagulants and oral hypoglycaemic agents.
- Other antiplatelet drugs such as clopidogrel and ticlopidine increase the risk of bleeding.
- Aspirin may enhance the effects of phenytoin and sodium valproate.
- The activity of methotrexate may be markedly enhanced by aspirin and its toxicity increased
- Aspirin may antagonise the diuretic effect of spironolactone and may reduce acetazolamide excretion (risk of toxicity).
- Aspirin increases plasma concentration of zafirlukast.
- Metoclopramide and domperidone enhance the effect of aspirin (increased rate of absorption).
- Avoid concomitant administration with mifepristone (theoretical interaction).
- Aspirin may inhibit action of uricosurics.
- The toxicity of sulphonamides may also be increased by aspirin.
- Aspirin is pharmaceutically incompatible with iron salts and alkalis.

Any toxicity relating to anti-tuberculosis drugs will be managed according to national guidelines (see national guidelines in Appendix D) or treatment procedures agreed by the hospital.

## Unblinding

Unblinding means revealing the identity of the study treatment (i.e. aspirin or placebo). Study treatment should only be unblinded if knowing the treatment that a patient has been allocated will result in a change in the patient’s management.

The decision whether or not to unblind should be discussed with the Principal Investigator when possible. Unblinded treatment allocation information will be available in opaque, tamper-proof envelopes held securely at each site and available at all times. The responsibility to approve unblinding will be assigned to dedicated site staff. Access to treatment allocation information should only be given with the approval of one of these dedicated staff. Unblinding will be documented in the case record form.

## Post-trial Treatment

Study medication will not be continued beyond the trial period of 60 days. Participants will continue standard care throughout the trial period and after the study treatment period is complete. Anti-tuberculosis treatment will be given thereafter for at least 6 months in line with national tuberculosis treatment guidelines. There are no restrictions on concomitant medicines once study treatment has stopped.

## Adverse events Management

Study treatment will be discontinued for all grade 3 and 4 events that are considered related to Aspirin use. For an event to be considered related it must follow a reasonable temporal sequence from trial medication administration and not reasonably be attributed to any other cause. Recognised adverse reactions to aspirin are listed in section 8.2 below. Study drugs will not be re-introduced in patients who have stopped treatment due to an adverse event. Management of adverse events will follow normal care and current practice guidelines.

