## Summary of Trial Design

The study is a parallel group, double blind, randomised, placebo controlled trial of 60 days of placebo vs. 81mg daily dose vs. 1000mg daily dose aspirin for the treatment of HIV-uninfected adults with tuberculous meningitis (see trial schema in appendix A). Patients will be recruited at the Hospital for Tropical Diseases (HTD), Ho Chi Minh City, Vietnam and should not have had more than 2 days of anti-tuberculosis chemotherapy or have received aspirin or any other NSAID within 2 weeks of randomisation. They should be able to have an MRI of their brain within 5 days of randomization.

Once enrolled, patients will be followed for 60 days and followed up at 8months for final outcome. They will all receive standard anti-tuberculosis chemotherapy and adjunctive dexamethasone (for 6-8 weeks), according to respective National Tuberculosis Programme guidelines (see attached guidelines for Viet Nam with this protocol). Participants will be stratified by site and MRC disease severity grade, and randomised on entry to one of three arms (1:1:1 ratio): aspirin 81mg, aspirin 1000mg or placebo daily for 60 days. Patients will be in-patients for at least the first 14 days of study treatment enabling real-time active surveillance of any adverse events after which they will be discharged according to clinical care. Study drug and standard treatment may be continued while patients are followed as out-patients.

Lumbar puncture will be performed before the start of treatment and then repeated in all patients on day 30 and 60 as per normal clinical care. Blood draws for pharmacokinetic assessment will be done 5 times between days 1 and 14. Assessment of peripheral blood monocyte/macrophage antimicrobial activity will be made at baseline and on day 240.

Clinical assessments will be performed at enrolment and weekly between day 7 and discharge. Brain magnetic resonance imaging (MRI) will be performed at baseline, day 60 and 240. A final clinical assessment of neurological disability will be made at 240 days.

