## Assessment of Adverse Events

Adverse events will be graded according to the Common Terminology Criteria for Adverse Events (CTCAE) definitions: <http://ctep.cancer.gov/protocolDevelopment/electronic_applications/ctc.htm>. In the event that an adverse event is not described within the CTCAE definitions, the following generic severity grading will be used:

**Grade 1 Mild;** asymptomatic or mild symptoms; clinical or diagnostic observations only; intervention not indicated.

**Grade 2 Moderate;** minimal, local or noninvasive intervention indicated; limiting age-appropriate instrumental Activities of Daily Living (ADL)*.

**Grade 3 Severe or medically significant but not immediately life-threatening;** hospitalization or prolongation of hospitalization indicated; disabling; limiting self care ADL**.

**Grade 4 Life-threatening consequences**; urgent intervention indicated.

*Instrumental ADL refer to preparing meals, shopping for groceries or clothes, using the telephone, managing money, etc.

**Self-care ADL refer to bathing, dressing and undressing, feeding self, using the toilet, taking medications, and not bedridden.

[Note: “Life-threatening” as a severity grade is not necessarily the same as “life-threatening” as a “serious” criterion used to define a serious adverse event. The former is a “potential” threat to life and the latter is an “immediate” threat to life.]

A laboratory abnormality only needs to be recorded as a clinical adverse event if it is associated with an intervention. Intervention includes, but is not limited to, discontinuation of a current treatment, dose reduction/delay of a current treatment, or initiation of a specific treatment. In addition, any medically important laboratory abnormality may be reported as an adverse event at the discretion of the investigator. This would include a laboratory result for which there is no intervention but the abnormal value suggests disease or organ toxicity. Laboratory events will be graded according to CTCAE definitions.

If clinical sequelae are associated with a laboratory abnormality, the diagnosis or medical condition should be reported as the adverse event (e.g., renal failure, haematuria) - not the laboratory abnormality (e.g., elevated creatinine, urine RBC increase).

The relationship of each adverse event to the trial medication must be determined by a medically qualified individual according to the following definitions:

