**Related**: The adverse event follows a reasonable temporal sequence from trial medication administration. It cannot reasonably be attributed to any other cause.

**Not Related**: The adverse event is probably produced by the participant’s clinical state or by other modes of therapy administered to the participant.

Patients will be under active surveillance for adverse events. All adverse events will be scored as not related, possibly related, or related to the study drug. The events listed below, and any others agreed between the treating doctor and Principal Investigator, are recognised adverse reactions to aspirin may be considered related to the trial intervention:

**Blood and lymphatic system disorders** - anaemia, haemolytic anaemia, hypoprothrombinaemia, thrombocytopenia, aplastic anaemia, pancytopenia, prolonged bleeding time, occult blood loss, elevated transaminase levels, agranulocytosis.

**Gastrointestinal disorders** - gastrointestinal bleeding, erosions, perforations or ulceration which can occasionally be major (may develop bloody or black tarry stools, severe stomach pain and vomiting blood), gastrointestinal irritation (mild stomach pain, heartburn, vomiting and nausea).

**Hepatic disorders** - hepatitis (particularly in patients with SLE or connective tissue disease)

**Renal and urinary disorders** – disturbances of renal function

**Ear and labyrinth disorders** - tinnitus

**Salicylism**- mild chronic salicylate intoxication may occur after repeated administration of large doses, symptoms include dizziness, tinnitus, deafness, sweating, nausea, vomiting, headache and mental confusion.

**General disorders and administration site conditions** – Allergic reactions: rhinitis, urticaria, purpura, Stevens-Johnson syndrome, angioneurotic oedema, angio-oedema, asthma, worsening of asthma, bronchospasms.

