## Adverse Event Recording

All adverse events which initiate after administration of the first dose of study drug and before the end of study day 60 will be recorded in the CRF. Events which are grade 3 and 4 adverse events and those judged to be possibly related or related to the trial intervention will be followed to resolution.

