## Regulatory Reporting of Adverse Events

As serious adverse events and mortality are common in tuberculous meningitis, safety reporting will focus on events of potential relevance to the trial intervention. The following events will be reported to the site ethical committee and the ethical committee of the Viet Nam Ministry of Health:

- All unexpected serious adverse events
- All serious adverse events judged to be related or possibly related to the trial intervention
- All deaths

Reporting to the ethical committees will include an initial written report, which will be sent as soon as possible and within 7 days of occurrence. The format and content of the initial report should follow the Viet Nam Ministry of Health report template and include all information available at the time of reporting. A follow up report with complete details will be sent within 15 days of the initial report if the initial report does not contain the details of event resolution.

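### The only mandatory adverse-event stop rests on a sole-cause attribution, so a severe gastrointestinal or cerebral bleed need not stop study drug

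*Protocol*

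**What the plan says.** **The stop.** Protocol 7.9 (Adverse events Management) states: "Study treatment will be discontinued for all grade 3 and 4 events that are considered related to Aspirin use". To count as related, an event must fit the timing of dosing and must "not reasonably be attributed to any other cause". The same paragraph refers the reader to the recognised aspirin reactions in 8.2, bars re-starting study drug after an adverse-event stop, and leaves management to normal care.

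**The causality scale.** Protocol 8.2 says that the relationship to trial medication "must be determined by a medically qualified individual according to the following definitions". Two definitions follow. Related repeats the sole-cause test. Not Related covers events probably due to the patient's clinical state or other therapy. The next paragraph uses three levels: "All adverse events will be scored as not related, possibly related, or related to the study drug". Events on the list that follows, and others that the treating doctor and Principal Investigator agree on, "are recognised adverse reactions to aspirin may be considered related to the trial intervention". The list includes GI bleeding, including major bleeds. It does not include cerebral bleeding.

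**Where the third level is used.** In 8.3, "Events which are grade 3 and 4 adverse events and those judged to be possibly related or related to the trial intervention" are followed until they resolve. In 8.4, the ethics committees receive "All serious adverse events judged to be related or possibly related to the trial intervention", as well as all unexpected serious adverse events and all deaths.

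**Discretion.** In 6.5 the investigator may stop study drug on any ground. The examples given include an aspirin-related serious adverse event and ineligibility that arises during the study.

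**The concern.** Bleeding is the harm that this pilot was set up to measure: the primary safety endpoint (5.2) is clinically significant upper GI bleeding or imaging-confirmed cerebral bleeding by day 60. One would expect the stop for a severe bleed to be firm. Instead it depends on a doctor, blind to allocation, deciding that nothing else could reasonably explain the bleed. These are severely ill patients who all receive anti-tuberculosis drugs and dexamethasone (5.1), so that decision will often be uncertain. The natural score for an uncertain case is possibly related, and 7.9 does not say what happens then.

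What is at stake is patient protection and consistency. Two doctors could follow the text correctly, score the same bleed differently, and one would have to stop a blinded antiplatelet drug while the other would not.

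**Working it through.** This is mainly a comparison of texts.

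**1. Levels defined and levels scored.** Section 8.2 defines two levels and scores three. The middle level can be inferred: an event with another reasonable but not probable cause meets neither definition, so it falls between them. The omission is therefore mostly one of drafting. Its direct effect is also narrow. Under 8.3 all grade 3-4 events are followed regardless, so the label matters only below grade 3. Under 8.4 it matters only for serious events that are neither unexpected nor fatal.

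**2. Consequence of each score for a grade 3-4 event.**

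| Score | Followed to resolution (8.3) | Ethics report if serious (8.4) | Study drug stopped |
| --- | --- | --- | --- |
| Related | yes | yes | required (7.9) |
| Possibly related | yes | yes | not stated in 7.9; permitted by 6.5 |
| Not related | yes | only if unexpected or fatal | permitted by 6.5 |

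A bleed can thus be reportable as possibly caused by study drug while no rule requires the drug to stop.

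**3. GI bleeding.** The 8.2 list, to which 7.9 refers, lets the doctor call a GI bleed related. The wording permits this and does not require it, and 7.9 keeps its sole-cause test alongside the reference.

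**4. Cerebral bleeding.** It is absent from the list and enters only if the treating doctor and Principal Investigator agree to add it. Section 9.1 recognises cerebral bleeding in TBM, though as extremely rare, so another cause can be named.

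**5. Number of patients who could be concerned.** Inputs from 9.1: 40 patients per arm; GI bleeding about 1% with no aspirin effect (3/278 = 1.08%, which reproduces the plan's rounded figure); a scenario of 10% in one aspirin arm; background cerebral bleeding below 0.01%. Setting the other two arms to 1% in the 10% scenario is my assumption.

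- 1% in every arm: 120 × 0.01 = 1.2 GI bleeds, of which placebo 40 × 0.01 = 0.4.
- 10% in one aspirin arm, 1% in the other two arms: 40 × 0.10 + 80 × 0.01 = 4.8.
- Cerebral bleeds at background: fewer than 120 × 0.0001 = 0.012. The document gives no rate on aspirin.

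The GI figures are expected counts at any grade, so the expected number at grade 3-4 is lower. The protocol gives neither the grade 3-4 share nor how often a bleed would be scored below related, so the number of missed stops cannot be computed.

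**The case against.** The strongest reply is that 7.9 should be read as a whole. Its relatedness test is followed directly by a pointer to a list that names GI bleeding, and the paragraph sends management to normal care. Section 6.5 allows a stop on any ground, and a bleeding patient fits several: suspected active GI bleeding, a history of GI bleeding, and aspirin considered contraindicated are all exclusions in 6.3, and ineligibility arising during the study is a listed reason. Section 7.7 also permits unblinding where it would change management. Most clinicians would stop the drug.

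All of this stands, and it limits the point. None of it turns the stop into an obligation. The list is permissive, 6.5 permits stopping without requiring it, and the protocol does not spell out what normal care means for study drug. The Data Safety Monitoring Board (8.5) reviews data on the first 30 patients, with later reviews at its discretion; it does not decide stops for individual patients.

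A further reply is that a cerebral bleed in TBM is so rare that attributing it to TBM would be unreasonable. That has some force, but the absence of cerebral bleeding from the list leaves the matter to the individual doctor.

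A reader might also infer that universal dexamethasone means a GI bleed can never pass the sole-cause test. The document does not support that. It nowhere says that dexamethasone alone causes bleeding; 12.4 places the added risk in adding aspirin to it; and 9.1 does not say whether the 278 patients behind the 1% figure received it. Co-exposure is not attribution, so the length of overlap with dexamethasone does not measure the gap.

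**Conclusion.** The point holds as a minor to moderate patient-safety gap. The single mandatory adverse-event stop uses a test that a severe bleed may fail, does not address possibly related events, and leaves cerebral bleeding off its supporting list. Stopping would often happen by discretion, but it is not required.

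Two stronger readings should be resisted. The protocol does not prevent stopping after a bleed; it only fails to require it. Nor is the primary safety result compromised: 5.2 and 9.2 count bleeds without any relatedness judgement, and patients are analysed in their randomised group.

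Few patients are involved: about 1.2 to 4.8 expected GI bleeds of any grade among 120 under the plan's own risks and the assumption stated for the other two arms. Confidence is high on what the text says. How often a stop would be missed in practice is unknown.

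**What to change.** In 7.9, require study drug to stop for any grade 3-4 GI bleed and any imaging-confirmed cerebral bleed, regardless of attribution. State there whether other grade 3-4 events scored possibly related trigger the stop or remain at the investigator's discretion.

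As a wording clean-up in 8.2, define possibly related: timing compatible with study drug, a contribution from aspirin not excluded, and another cause also reasonable. Carry that definition onto the case report form.

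The cost is protocol text and one form definition, with no added procedures. A few more patients would stop, some of them on placebo, and under 7.9 they would not restart. The expected total is bounded by the 1.2 to 4.8 GI bleeds above (0.4 of them on placebo at 1%) plus any cerebral bleeds, and some of these patients would have stopped anyway. Continued follow-up after a stop (6.5) and analysis by randomised group (9.2) keep their data in the trial.
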